## Abstract

**Background:** Malnutrition and cachexia are common in patients with advanced pancreatic ductal adenocarcinoma (PDAC) and have a significant influence on the tolerance and response to treatments. If timely identified, malnourished PDAC patients could be treated to increase their capacity to complete the planned treatments and, therefore, possibly, improve their efficacy.

**Aims:** The aim of this study is to assess the impact of nutritional status, pancreatic exocrine insufficiency (PEI), and other clinical factors on patient outcomes in patients with advanced PDAC.

**Methods:** PAncreatic Cancer MAlnutrition and Pancreatic Exocrine INsufficiency in the Course of Chemotherapy in Unresectable Pancreatic Cancer (PAC-MAIN) is an international multicenter prospective observational cohort study. The nutritional status will be determined by means of Mini-Nutritional Assessment score and laboratory blood tests. PEI will be defined by reduced fecal elastase levels. Main outcome: adherence to planned chemotherapy in the first 12 weeks following the diagnosis, according to patients' baseline nutritional status and quantified and reported as “percent of standard chemotherapy dose delivered.” Secondary outcomes: rate of chemotherapy-related toxicity, progression-free survival, survival at 6 months, overall survival, quality of life, and the number of hospitalizations. Analysis: chemotherapy dosing over the first 12 weeks of therapy (i.e., percent of chemotherapy received in the first 12 weeks, as defined above) will be compared between well-nourished and malnourished patients. Sample size: based on an expected percentage of chemotherapy delivered of 70% in well-nourished patients, with a type I error of 0.05 and a type II error of 0.20, a sample size of 93 patients per group will be required in case of a percentage difference of chemotherapy delivered of 20% between well-nourished and malnourished patients, 163 patients per group in case of a difference of 15% between the groups, and 356 patients per group in case of a 10% difference. Centers from Russia, Romania, Turkey, Spain, Serbia, and Italy will participate in the study upon Local Ethics Committee approval.

**Discussion:** PAC-MAIN will provide insights into the role of malnutrition and PEI in the outcomes of PDAC. The study protocol was registered at clinicaltrials.gov as NCT04112836.

## Background

Pancreatic ductal adenocarcinoma (PDAC) represents one of the most lethal malignancies nowadays (1), with an age-standardized incidence rate of 4.8 and age-standardized mortality of 4.4 per 100,000 people worldwide. PDAC accounts for the majority of cases of pancreatic neoplasms (2). Diagnostic and therapeutic advancements led to a decrease in mortality of the most cancer types during the last decades; however, PDAC mortality still almost equals the incidence (1), with 5-year survival lower than 10% in the United States (3). The fact that most PDAC patients remain asymptomatic until advanced stages of the disease, as well as the aggressive biological behavior of this tumor and the absence of an effective screening method, largely contribute to these results. However, taking into account that more than 450,000 persons each year are diagnosed with PDAC (1) representing significant healthcare and socioeconomic burden, there is a substantial need for improvement in the diagnostics and therapy in order to prolong survival.

A profound weight loss is one of the early symptoms of PDAC that can precede the diagnosis by months (4). Cachexia, as a symptom and consequence of the disease course, is present in many cancer types, especially in the late stages. Fearon et al. (5) described it as a multifactorial syndrome defined by an ongoing loss of skeletal muscle mass (with or without loss of fat mass) that cannot be completely reversed by conventional nutritional support and leads to progressive functional impairment. In addition to changes such as skeletal muscle wasting or loss of adipose tissue, cachexia is associated with changes in numerous nutritional parameters (6). Among the mechanisms determining the tumor-induced cachexia, the breakdown of molecules due to increased catabolism and inflammation are considered very important (7). Moreover, it has been recently reported that altered pancreatic exocrine function can additionally contribute to cachexia in pancreatic cancer by driving adipose tissue wasting (8).

Cachexia and malnutrition not only represent symptoms of the disease but also are important factors having a significant impact on the outcome of PDAC patients (9). A low value of fecal elastase-1, depicting impaired exocrine pancreatic function and contributing to cachexia, has been reported to strongly correlate with poor survival in advanced PDAC patients (10). However, cachexia and impaired nutritional status might also affect the tolerance and response to medical treatments such as chemotherapy. This is particularly important in PDAC; not more than 20% of patients are eligible for the resection at the time of the diagnosis (3), while the rest might have an indication for chemotherapy. In this setting, while Gemcitabine mono-chemotherapy has for a long time been the standard treatment for unresectable PDAC with relatively poor effect represented by a median overall survival (OS) around 6 months (11), intensified regimens, such as the combination of 5-fluorouracil, leucovorin, irinotecan, and oxaliplatin (FOLFIRINOX), or the addition of Nab-Paclitaxel to gemcitabine, are nowadays more frequently used, with substantially improved survival (12–17). However, due to their side effects, particularly encountered in FOLFIRINOX, intensified regimens can be less tolerable, leading to dose reduction or therapy discontinuation (13–15), which makes their use limited to the patients with ECOG status of 0, 1, and 2 (15, 16). For patients with ECOG of 3 or higher, the large majority of experts recommend best supportive care (18).

Considering this, it is even more important to assess the impact of the nutritional status in patients with advanced PDAC in order to identify sub-groups at a higher risk of side effects and treatment discontinuation. If timely identified, these patients could be approached and treated accordingly, in order to increase their capacity to complete the planned therapy and therefore possibly improve its efficacy. Studies so far conducted to address this important issue have been too few and limited in terms of parameters evaluated as well as outcomes observed and often did not use standardized measures. Hence, evidence is sparse and heterogeneous.

We, therefore, designed a multicenter prospective study in order to assess the impact of patient's nutritional status on the clinical course of advanced PDAC patients receiving chemotherapy.

### Hypothesis

We hypothesize that malnutrition has an adverse impact on the clinical course of patients with advanced PDAC treated with chemotherapy.

### Aims

To investigate the association between the nutritional status and pancreatic exocrine function and the clinical outcomes of patients with advanced PDAC.

## Methods

### Study Design

The PAncreatic Cancer MAlnutrition and exocrine pancreatic INsufficiency in the course of chemotherapy in unresectable pancreatic cancer (PAC-MAIN) study is a non-profit, international, multicenter, prospective, observational, cohort study evaluating the effect of the nutritional status and pancreatic exocrine function on the main outcomes of patients with advanced PDAC. The study will be carried out in Russia, Turkey, Serbia, Romania, Italy, and Spain as a part of the Pancreas 2000 Educational Program. Pancreas 2000 is a post-graduate educational program that prepares young gastroenterologists, surgeons, radiologists, and other physicians for specialization in Pancreatology (19).

#### Patients

Population: patients with unresectable locally advanced or metastatic PDAC attended in each participant's center.

Inclusion criteria:

age ≥ 18 years;histological diagnosis of PDAC within 1 month from recruitment to the study;radiological diagnosis of the advanced stage not suitable for upfront surgical resection (either locally advanced or metastatic) within 5 weeks from recruitment to the study (20);a written consent to participate in the study;being planned for chemotherapy.

The following exclusion criteria will be applied:

poor performance status (Eastern Cooperative Oncology Group scale (ECOG) ≥ 3) (18)^1^;pregnancy;past history of any anticancer treatment (surgery and/or chemotherapy);enteral nutrition.

#### Variables

The following variables will be recorded in a dedicated Case Report Form (CRF).

All these measures are part of a standard workup of advanced PDAC patients and considered good clinical practice.

Patient-related:sex, race, age at diagnosissignificant comorbidities: chronic kidney failure, chronic heart failure, or respiratory insufficiency requiring oxygen treatmentMini-Nutritional Assessment (MNA) score. Primarily developed for elderly patients, MNA score was successfully used in the PreMiO study (Prevalence of malnutrition in patients at first medical oncology visit) to identify the risk of malnutrition or malnutrition among cancer patients at their first medical oncology visit (21):◾ 0–7 points: Malnourished◾ 8–11 points: At risk of malnutrition◾ 12–14 points: Normal nutritional statussarcopenia [measured with computed tomography (CT); fat-free mass is reduced; i.e., appendicular/L2 skeletal muscle mass index < 7.2 kg/m^2^ (men) or <5.5 kg/m^2^ (women)];cachexia [weight loss (WL) > 5% in the last 6 months, or WL > 2% if body mass index (BMI) < 20 kg/m^2^ or sarcopenia];12-item functional assessment of anorexia/cachexia therapy anorexia/cachexia subscale (FAACT-A/CS-12)a biliary stenta duodenal stenttotal and direct bilirubinECOG statusEuropean Organization for Research and Treatment of Cancer (EORTC) QLQ-PAN26 scale (22)Date of diagnosis, visit 1, visit 2 (3 months), and death/loss from follow-upCheck up on survival at 6 m

Tumor-related:Tumor site documented by endoscopic ultrasound, CT, or magnetic resonance imaging (head, body, or tail)Stage according to the TNM classificationVessels involvedPresence and site of metastatic diseaseAscitesCA-19-9Response evaluation criteria in solid tumors (RECIST) (23) (for visit 2)

Nutritional parameters:Leucocytes (lymphocytes, neutrophils), neutrophil-to-lymphocyte ratio, erythrocytes, hemoglobin, hematocrit, plateletsC-reactive protein, total protein, albumin, cholesterol, iron, transferrin, ferritin, magnesium, zincInternational normalized ratio, activated partial thromboplastin timeBlood fasting glucose, glycated hemoglobin

Pancreatic function and treatment:PEI will be defined by levels of fecal elastase-1 <200 mcg/g; pancreatic enzyme replacement therapy (PERT), date of starting PERT, the dosage of daily taken PERTDiabetes mellitus (DM), date of DM diagnosis, DM type, DM treatment

Treatment-related:Planned chemotherapy protocolDosages of chemotherapy planned (mg/m^2^)Percent of standard chemotherapy dose deliveredPercent of planned chemotherapy deliveredChanges to the predefined schedule (dose reduction, schedule modifications, stop before planned)Date of treatment start and endAdverse events (National Cancer Institute toxicity scale for visit 2) (24).

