#### Outcomes

The association between all the abovementioned variables and the following outcome variables will be assessed:

Primary outcome:

Adherence to planned chemotherapy in the first 12 weeks after the diagnosis in patients' groups stratified according to their baseline nutritional status.

Drug doses will be expressed in weight-based, body surface area (BSA)-based, AUC units or flat dose, according to standard dosing practice for a given drug or combination. For each drug in a regimen, the sum of the doses delivered during the first 12 weeks of therapy will be divided by the sum of the expected doses based on published standard schedule and dosing. The mean percent dose delivered of all drugs in a regimen will be reported as “percent of standard chemotherapy dose delivered.”

Similarly, the sum of the doses delivered during the first 12 weeks of therapy will be divided by the sum of the expected doses based on each patient's starting chemotherapy dose, and the mean percent dose delivered for all drugs in a regimen will be reported as “percent of planned chemotherapy delivered.” We will use percent of standard chemotherapy dose delivered to estimate the overall relative dose delivered, and we will use percent of planned chemotherapy dose delivered to quantify further dose reductions from starting dose and as an indicator of overall toxicity.

Secondary outcomes:

Percent of patients with chemotherapy-related toxicity in each group of patientsOS and survival at 6 monthsProgression-free survivalQuality of life that will be assessed using the European Organization for Research and Treatment of Cancer (EORTC) QLQ-PAN26 scaleNumber of hospitalizationsFactors associated with the percent of chemotherapy received.

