#### Description of the Intervention (Schedule of Visits)

Visit 1 (screening, within 1 month from initial diagnosis)

Patients will be informed about the study. Once patients agree with the inclusion in the study, we will evaluate the inclusion and exclusion criteria. Those patients who meet all the inclusion criteria and none of the exclusion criteria will be finally included in the study. In this visit, patient-related, tumor-related, and pancreatic function and treatment-related variables will be recorded, and quality of life questionnaire will be administered. The researcher will record weight, height, BMI, and unplanned WL % for the last 6 months.

Each patient's baseline nutrition status will be evaluated using the MNA score prior to starting chemotherapy. Patients will be classified as in the group with no nutritional risk, at risk of malnutrition, or malnourished.

Nutritional parameters and pancreatic function will be evaluated through blood tests and a fecal test.

Visit 2 (3 months after the first dose of planned chemotherapy)

The researcher will record in the CRF the planned chemotherapy, schedule, doses, dose reduction, and any adverse event^1^. The same variables recorded at Visit 1 will be checked again.

Check-up 3 (end of the study, 6 months)

The researcher will record in the CRF the OS and time until progression.

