Multivariable logistic regression analysis will be used to estimate the independent effect of malnutrition status on percent chemotherapy received (<80% chemotherapy received vs. 80% chemotherapy received; binary end point), after controlling for demographic and clinical characteristics (age, sex, race, ECOG status, tumor site, tumor stage, PEI, and DM). The demographic and clinical variables included in the final model will be chosen using a forward-stepwise method. Similarly, multivariable linear regression analysis will be used to estimate the independent effect of nutritional status on mean percent chemotherapy received (i.e., continuous endpoint), after controlling for demographic and clinical characteristics. All *p* values are two-sided with statistical significance evaluated at the 0.05 alpha level. Ninety-five percent confidence intervals (CIs) will be calculated to assess the precision of the obtained estimates (for odds ratios/beta estimates). The Kaplan–Meier method will be used to estimate OS and progression-free survival (PFS). The log-rank test will be used to compare OS and PFS between well-nourished patients and malnourished patients. Greenwood's formula will be used to calculate 95% CIs for Kaplan–Meier survival estimates. The frequency and percentage of missing values for each variable will be collected, analyzed, and reported (missing value analysis). All data will be anonymous once data collection is completed, respecting the confidentiality of the subjects participating, in accordance with data protection laws. All analyses will be performed in STATA 14 (Statacorp LLC, Texas).

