#### Power Size Calculation

The expected percent of chemotherapy delivered in well-nourished patients was based on a study that assessed the chemotherapy dose intensity in gastrointestinal malignancies that included pancreaticobiliary disease during the first 8 weeks after the start of the chemotherapy (25). Based on an expected percentage of chemotherapy delivered of 70% in well-nourished patients, with a type I error of 0.05 and a type II error of 0.20, a sample size of 93 patients per group will be required in case of a percentage difference of chemotherapy delivered of 20% between well-nourished and malnourished patients, 163 patients per group in case of a difference of 15% between both groups, and 356 patients per group in case of 10% difference.

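### The CT-based sarcopenia rule applies one kg/m² cut-off per sex to both limb muscle mass and an L2 measure with no stated conversion, so its L2 part cannot classify patients as written

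*Protocol article*

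**What the plan says.** In the protocol article, Methods, Variables, sarcopenia is to be measured by CT and is described as reduced fat-free mass. The operational rule for men is "appendicular/L2 skeletal muscle mass index < 7.2 kg/m^2^ (men" and for women "or <5.5 kg/m^2^ (women". Each sex thus has one threshold, in kg/m², shared by an appendicular index and an L2 index. The article gives no conversion from a CT measurement to kilograms and no separate L2 threshold.

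The same list uses sarcopenia inside cachexia, which is weight loss above 5% in six months, "or WL > 2% if body mass index (BMI) < 20 kg/m^2^ or sarcopenia".

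The Outcomes section commits to using these variables: "The association between all the abovementioned variables and the following outcome variables will be assessed". It also lists predictors of the chemotherapy dose received as a secondary outcome.

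The main exposure is a different variable. In the schedule of visits, "Each patient's baseline nutrition status will be evaluated using the MNA score prior to starting chemotherapy". The adjustment variables named under Statistical Analysis are "age, sex, race, ECOG status, tumor site, tumor stage, PEI, and DM", which include neither sarcopenia nor cachexia.

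**The concern.** Three quantities share one pair of thresholds: fat-free mass, limb muscle mass, and muscle at a lumbar level. They are not interchangeable. The first two are masses. The third, taken from a CT slice, is an area. A threshold in kg/m² has no direct meaning for an area index, and a slice at L2 does not contain the limbs that the appendicular index refers to.

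A centre that follows the text must therefore supply its own reading. The study runs in six countries. If centres choose differently, the sarcopenia class partly records which centre the patient attended, and its association with dose delivered, toxicity or survival is mixed with centre differences. Because cachexia uses sarcopenia as one of its criteria, part of that class inherits the problem. The Background presents cachexia and muscle loss as a main reason for the study, so these associations matter even though they are not the primary comparison.

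**Working it through.** The plan states no prevalence of sarcopenia, so there is no figure of its own to reproduce. The check is one of units, followed by a check of how far the problem reaches.

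**Inputs from the article.** Cut-offs 7.2 kg/m² (men) and 5.5 kg/m² (women); CT as the method; the cachexia rule.

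**Assumed inputs, not in the article.** L2 means the second lumbar vertebra. Muscle area A is 60–200 cm², height h is 1.55–1.85 m, muscle density is 1.06 g/cm³, and slice thickness t is 0.1–1.0 cm. The ranges are deliberately wide.

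**Reading 1: area index compared with the cut-off as bare numbers.** Index = A/h².
- Lowest: 60/1.85² = 60/3.4225 = 17.5 cm²/m².
- Highest: 200/1.55² = 200/2.4025 = 83.2 cm²/m².
- The lowest value is 17.5/7.2 = 2.4 times the male cut-off and 17.5/5.5 = 3.2 times the female one.
- With a narrower range (90–160 cm², 1.6–1.8 m) the index runs from 90/1.8² = 27.8 to 160/1.6² = 62.5. The lowest value is then 27.8/7.2 = 3.9 and 27.8/5.5 = 5.1 times the cut-offs.

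Nobody falls below the cut-off, so nobody is sarcopenic.

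**Reading 2: the slice taken as a mass.** Index = A × t × 1.06/1000/h².
- Lowest: 60 × 0.1 × 1.06/1000/3.4225 = 0.002 kg/m².
- Highest: 200 × 1.0 × 1.06/1000/2.4025 = 0.088 kg/m².

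Everybody falls below both cut-offs, so everybody is sarcopenic.

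**How far a slice is from the threshold.** The depth of muscle of the measured area needed to reach the cut-off c is c × h² × 1000/(1.06 × A) cm.
- For 7.2: from 7.2 × 2.4025 × 1000/(1.06 × 200) = 82 cm to 7.2 × 3.4225 × 1000/(1.06 × 60) = 387 cm.
- For 5.5: from 62 cm to 296 cm by the same formula.

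No slice thickness bridges the gap. Only a conversion equation would, and none is stated.

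**Reach into cachexia**, reading sarcopenia as the alternative to low BMI within the 2% criterion:

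| Weight loss | BMI | Does sarcopenia decide cachexia? |
|---|---|---|
| above 5% | any | No, cachectic already |
| above 2% to 5% | below 20 | No, cachectic already |
| above 2% to 5% | 20 or more | Yes, entirely |
| 2% or less | any | No, not cachectic |

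Reading 1 makes every patient in the third row non-cachectic; Reading 2 makes every one cachectic. The article does not say how many patients fall in that row.

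**Reach into the primary analysis.** The groups compared are defined by MNA. The sample size uses an expected 70% dose delivered, differences of 20, 15 and 10 points, and error rates given as "with a type I error of 0.05 and a type II error of 0.20". Sarcopenia is an input to neither.

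**The case against.** The strongest defence is that this is a condensed article. The wording can be read as a mass index estimated from the L2 slice, which fits the mention of fat-free mass and a mass index. The equation from CT area to kilograms could then sit in the case report form or the full protocol, which are not shown. This stands in part: such a conversion would make the printed cut-offs usable, and the article does not show that the measure is impossible. It does not remove the point, because the article itself fixes modality, measure, threshold and unit, and these do not fit together as printed. That is a definition stated badly, not a detail left out.

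Three stronger conclusions are tempting, and the document supports none of them.
- **Sarcopenia prevalence will be 0%.** This follows only if centres compare cm²/m² with kg/m² as bare numbers. The slice-as-mass reading gives the opposite extreme, and the article prescribes neither.
- **The whole cachexia class is wrong.** Only weight loss above 2% and up to 5% with BMI of 20 or more depends on sarcopenia.
- **The main result is undermined.** The primary comparison uses MNA, and neither sarcopenia nor cachexia is among the named covariates.

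**Conclusion.** The point holds as a defect in a secondary definition that should be corrected. The L2 part of the sarcopenia rule cannot be applied as printed. Under the assumed ranges, the share of patients below the cut-off is none or all, depending on a reading that the article leaves open. Those two extremes show that the rule is undetermined; they do not predict what centres will do. If a conversion is in use, the result could lie anywhere between them.

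The dimensional mismatch itself needs only that a CT slice measures area and that L2 is a lumbar level. The none-or-all figures also rest on the assumed areas, heights, density and slice thickness. The analyses at risk are the planned associations of sarcopenia, and of cachexia in the band identified above, with the outcomes.

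**What to change.** In the protocol and the case report form, name one CT measure at one vertebral level. Then do one of the following:
- give sex-specific cut-offs derived for that measure, in its own units;
- analyse the measure as a continuous, sex-standardised index;
- keep the printed kg/m² cut-offs and state the validated conversion that makes them applicable.

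The article does not supply a cut-off in area units, so none is suggested here. If the continuous option is chosen, the cachexia rule still needs a stated yes/no definition of sarcopenia. Derive cachexia from the corrected variable, in the same way at all centres.

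Report patients without a usable CT as missing for sarcopenia, and for cachexia where it depends on sarcopenia. This may occur: the inclusion criteria ask for a radiological diagnosis without naming CT, and tumour site may be documented by endoscopic ultrasound or MRI.

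The cost is one revised definition and possibly some missing values. CT is already the method specified for sarcopenia, so the change adds no new type of measurement, and it leaves the primary comparison and sample size as they are.

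### Exocrine function, one of the study's two named exposures, is specified for the models only as PEI yes/no at 200 mcg/g, although a continuous elastase level underlies it

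*Protocol article*

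**What the plan says.** Under Study Design, the protocol article describes a cohort study "evaluating the effect of the nutritional status and pancreatic exocrine function on the main outcomes of patients with advanced PDAC". Aims likewise puts exocrine function beside nutritional status.

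Under Variables, "PEI will be defined by levels of fecal elastase-1 <200 mcg/g". Elastase appears there only inside that definition, whereas CA-19-9, albumin, glycated hemoglobin and bilirubin are listed as variables in their own right.

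Under Statistical Analysis, the logistic model for receiving less than 80% of chemotherapy draws its covariates from "age, sex, race, ECOG status, tumor site, tumor stage, PEI, and DM", and those in the final model "will be chosen using a forward-stepwise method". The linear model for mean percent received is introduced as similar, with its covariates described only in general terms.

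Two other sentences bear on the point. Outcomes says "The association between all the abovementioned variables and the following outcome variables will be assessed". The schedule of visits says "Nutritional parameters and pancreatic function will be evaluated through blood tests and a fecal test". Neither gives a scale for elastase.

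**The concern.** A yes/no split treats a patient just under 200 mcg/g and one with almost no elastase as the same, and treats two patients just either side of 200 as different. If risk changes gradually with elastase, this costs power for one of the two exposures, and a real association could be read as absent.

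There is a second consequence for the malnutrition estimates. Background says: "A low value of fecal elastase-1, depicting impaired exocrine pancreatic function and contributing to cachexia, has been reported to strongly correlate with poor survival". The authors thus place exocrine function upstream of nutritional status and relate it to an outcome. The multivariable models claim an independent effect of malnutrition. With PEI as a two-level covariate, differences in elastase within each level stay unadjusted, and part of any effect of exocrine failure could be credited to malnutrition.

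**Working it through.** **The plan's own figure.** The only computed figure is the sample size, and it concerns malnutrition, not elastase. Using two proportions, pooled variance, two-sided alpha 0.05, power 0.80 and no continuity correction:

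n per group = [1.960·√(2·p̄(1−p̄)) + 0.8416·√(p1(1−p1) + p2(1−p2))]² / (p1−p2)²

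- 70% v 50%: (1.358 + 0.571)² / 0.04 = 93
- 70% v 55%: (1.342 + 0.569)² / 0.0225 = 163 (rounded up)
- 70% v 60%: (1.322 + 0.565)² / 0.01 = 356

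All three match Power Size Calculation, and nothing below changes them.

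**Information kept by the cut.** The documents give no PEI prevalence, elastase distribution or correlation with MNA, so the following assumes a normalised level (for example log elastase) with a linear effect. With a share q of patients below the cut, the share of information kept is r² = φ(z_q)² / [q(1−q)].

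| q below 200 | φ(z_q) | kept | lost |
|---|---|---|---|
| 0.50 | 0.399 | 0.637 | 36% |
| 0.40 or 0.60 | | 0.622 | 38% |
| 0.30 or 0.70 | | 0.576 | 42% |
| 0.25 or 0.75 | 0.318 | 0.539 | 46% |
| 0.20 or 0.80 | 0.280 | 0.490 | 51% |
| 0.10 or 0.90 | | 0.342 | 66% |

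**Illustration in power.** Assume 4 percentage points of dose per SD of log elastase and a residual SD of 28. Neither is in the documents. Power ≈ Φ(z − 1.96), where z = 4 / (28/√N), multiplied by √r² for the cut.

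For N = 2 × 163 = 326, z = 2.58.
- Continuous: Φ(0.62) = 73%.
- Half below 200: 2.58 × 0.798 = 2.06, power 54%.
- 75% below 200: 2.58 × 0.734 = 1.89, power 47%.

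For the other two planned sizes:
- N = 186 (2 × 93), z = 1.95: 50% falls to 34% or 30%.
- N = 712 (2 × 356), z = 3.81: 97% falls to 86% or 80%.

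**Residual confounding.** Let ρ be the correlation of elastase with the nutrition measure (assumed). The share of the crude bias left after adjusting for the binary version is (1−r²) / (1−ρ²r²).
- q = 0.50, ρ = 0.2: 0.363 / 0.975 = 37%
- q = 0.50, ρ = 0.5: 0.363 / 0.841 = 43%
- q = 0.30 or 0.70, ρ = 0.2: 0.424 / 0.977 = 43%
- q = 0.30 or 0.70, ρ = 0.5: 0.424 / 0.856 = 50%

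A simulation agrees. It assumed 5 points of dose per SD, a log-odds slope of 0.8 for malnutrition and no true malnutrition effect. The crude bias of about −3.4 points fell to about −1.3 (half below 200) or −1.7 (75% below) with binary PEI, and to about 0 with the continuous level. That zero is by construction, because the simulated effect was linear in the variable adjusted for.

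**The case against.** The quoted definition is diagnostic; it does not say how the level will be analysed. Nothing bars use of the elastase value, and Outcomes promises to relate every recorded variable to the outcomes. PEI is named only as a candidate in the logistic model, the linear model's covariates are not itemised, and a condensed article may leave covariate scale to a fuller plan. A reader might therefore infer that elastase is used only as a yes/no class throughout; the documents do not go that far. They do choose a form: PEI is what Variables defines and what the covariate list names. That choice can be assessed as written.

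The numerical case rests on outside assumptions: normality, linearity, the share below 200, the effect sizes, the residual SD and the link with MNA. That objection stands, so the figures are a conditional range. The loss is smaller if the effect is a step at 200.

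The causal premise is also incomplete. Background links exocrine function to cachexia and to survival, but gives no effect on chemotherapy dose apart from nutrition. Confounding of the dose outcome is plausible and not shown.

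Finally, forward-stepwise selection may drop the term on any scale. That is a separate weakness, but rescaling alone would not secure the adjustment.

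**Conclusion.** The point holds as a modest, inexpensive improvement. For a named exposure the protocol specifies a two-level model term where a continuous level underlies it. With a linear effect of a normalised level and 20% to 80% of patients below 200 mcg/g, about 36% to 51% of the information is lost; at 10% or 90% below, 66%.

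Three stronger readings are tempting and are not supported:
- **That the malnutrition estimate is simply left confounded.** Under the assumptions tried (30% to 70% below the cut, correlation 0.2 to 0.5), binary PEI already removes about half to 63% of the linear bias. What remains is residual, and its absolute size is unknown.
- **That the loss is largest if most patients fall below 200.** It is smallest at an even split and only 38% with 60% below; it grows as the split becomes extreme in either direction.
- **That the main result is at risk.** The two-sample comparison of percent chemotherapy between nutrition groups does not involve PEI, so only the exocrine-function analyses and the adjusted models are affected.

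**What to change.** - Keep the 200 mcg/g threshold to describe PEI prevalence and as a secondary presentation of results.
- Confirm that the CRF stores the numeric Visit 1 fecal elastase-1 value; Variables does not list it separately.
- In the exocrine-function association analyses and in both the logistic and the linear model, enter that value as a continuous term, on the log scale or as a 3-knot restricted cubic spline. The spline would also help show whether the relation is gradual or closer to a step.
- Retain this term in both models regardless of forward-stepwise selection.

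The cost is a few sentences of analysis wording and possibly one CRF field, since the fecal test is already planned. Sample sizes do not change. The coefficient is less familiar to clinicians than PEI yes/no, which can be reported beside it, and a 3-knot spline uses one more degree of freedom than the binary term.
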